### Methods for additional analyses (e.g., subgroup analyses) {21b}

Additional subgroup analyses will be performed for gender (male/female), age group (individuals up to 60 years old/individuals 60 years old or older), and severity of the disease at the randomization time (less severe presentation: patient in ambient air or using O_2_ in catheter; more severe presentation: use of O_2_ high flow, NIV, MV, or ECMO).

The analysis of all these subgroups for the primary endpoint will be done using the Cox proportional hazards model. A mortality analysis will also be performed on each of these subgroups using the logistic regression model. The analysis of all the subgroups mentioned here will be performed for the comparison of both icatibant plus standard care vs. standard care alone and for the comparison of C1 esterase Inhibitor plus standard care vs. standard care alone.

### Methods of analysis to handle protocol non-adherence and any statistical methods to handle missing data {21c}

We will use multiple imputation for missing data. A per-protocol analysis will be used to check the robustness of the results obtained primarily by the intention-to-treat principle.

### Plans to give access to the full protocol, participant-level data, and statistical code {31c}

After the study has ended, we intend to make available the full protocol and the statistical code through scientific publication.

### Composition of the data monitoring committee, its role, and reporting structure {21a}

Given that this study is of high interest to the scientific community within the context of the pandemic and that it may deeply affect the clinical practice, we have chosen to adopt a Data Safety Monitoring Committee (DSMC). In addition, there are concerns regarding the use of experimental drugs in the specific condition studied. The DSMC will aim to assess the continuing validity of the trial (critical efficacy endpoints), monitor adverse events, ensure clinical equipoise, and monitor protocol compliance, data quality, and participant recruitment. The DSMC will be composed of clinicians, the study sponsor, and at least one biostatistician. The agenda of group meetings and the template to be followed will be defined by the team itself. This committee will have an advisory role and is composed of [name] and [name].

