## Assignment of interventions: blinding

### Who will be blinded {17a}

This is an open-label trial because neither the trial participant nor the care providers will be blinded. However, the data entry staff and data manager will be blinded. The data will be sent to the data entry staff by code, and the study arm will not be specified. The data entry staff and data managers are not part of the hospital staff and will not have access to any clinical data belonging to the patients. The Data Safety Monitoring Board (DSMC) will be unblinded.

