### Interim analyses {21b}

We will perform an interim analysis for effectiveness, futility, and safety when we have reached 50% of the events between all groups (three arms).

The Cox proportional hazards model will be used to evaluate the primary outcome in this interim analysis. The logistic regression model will be used to evaluate the occurrence of severe adverse events as a secondary endpoint.

An independent statistician will perform the interim analyses, and the results will be evaluated by the DSMC.

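### The study sponsor is a named member of the unblinded committee that evaluates interim efficacy, so as written it would see arm-level results with half the events still to accrue

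*Protocol article*

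**What the plan says.** Four parts of the protocol article bear on this.

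- **Composition of the data monitoring committee {21a}.** "The DSMC will be composed of clinicians, the study sponsor, and at least one biostatistician". The sponsor is listed on the same footing as the other members, with no mention of observer status or limited attendance. The remit includes efficacy: "The DSMC will aim to assess the continuing validity of the trial (critical efficacy endpoints), monitor adverse events, ensure clinical equipoise". On authority: "This committee will have an advisory role".
- **Who will be blinded {17a}.** "The Data Safety Monitoring Board (DSMC) will be unblinded". No member is excepted. The section uses the word Board, but the abbreviation is that of the committee in {21a}. Of the trial: "This is an open-label trial because neither the trial participant nor the care providers will be blinded". Data entry staff and data managers, by contrast, are kept unaware of the study arm.
- **Interim analyses {21b}.** One look is planned for efficacy, futility and safety, at 50% of the events counted over all three arms. "The Cox proportional hazards model will be used to evaluate the primary outcome in this interim analysis". "An independent statistician will perform the interim analyses, and the results will be evaluated by the DSMC".
- **Statistical methods for primary and secondary outcomes {20a}.** The analysis plan is to be completed and given to the committee ahead of the final analysis. Nothing there requires it to be complete before the interim look.

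**The concern.** An independent statistician is used at an interim analysis so that the comparative result stays with people who have no stake in the trial and no hand in its remaining course. Here the analysis is produced independently but then delivered to a committee that includes the sponsor.

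Two things are at stake. The first is confidentiality. Once the sponsor knows how the arms compare, that knowledge can colour later decisions within its reach, such as recruitment effort, amendments, or analysis choices if the plan is still open. The second is the standing of the committee's advice. A recommendation to stop for efficacy or futility, or to continue, is easier to challenge if a party with an interest in the answer helped to form it.

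**Working it through.** **Does the text put arm-level results in front of the sponsor?**

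1. The sponsor is a member of the committee ({21a}).
2. The committee is unblinded, without exception ({17a}).
3. The committee evaluates the interim results ({21b}), and these include a Cox model of the primary outcome ({21b}).
4. No section available limits the sponsor to open sessions, makes it non-voting, or requires members to be independent of it.

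Steps 1 to 3 are all explicit, so the conclusion needs no inference beyond reading them together. The independent statistician governs who produces the analysis, not who receives it.

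**How much of the trial is still to come?** Half, directly from the 50% trigger. Event counts only illustrate this.

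Inputs, from Sample size {14}: hazard ratio 1.9, power 80%, alpha 2.5% per comparison (taken as two-sided), censoring 20%, multiplier 1.5 for three arms, total 174.

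The plan's own figure, by Schoenfeld's formula for one comparison with control:

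- Events = (2.241 + 0.842)² / (0.25 × (ln 1.9)²) = 92.3
- Patients, two arms = 92.3 / 0.80 = 115.4
- Three arms = 1.5 × 115.4 = 173.0. Rounding up to 58 per arm gives 3 × 58 = 174, as stated.

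Events at the look, assuming that the 20% censoring is the only source of non-events and is equal over arms:

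| | N = 174 (Sample size {14}) | N = 180 (Abstract) |
|---|---|---|
| Events, three arms (0.8 × N) | 139.2 | 144 |
| At the interim (half) | 69.6 | 72 |
| Still to accrue | 69.6 | 72 |
| Events per comparison, final (two-thirds) | 92.8 | 96 |
| Events per comparison, interim | 46.4 | 48 |

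**How informative is that look?** With 46.4 events in a comparison, the standard error of the log hazard ratio is about √(4/46.4) = 0.294. An observed hazard ratio of 1.9 would carry a nominal 95% interval of exp(0.642 ± 1.96 × 0.294), about 1.07 to 3.38. That is enough to shape opinion about an arm, and far from a final answer.

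**The case against.** The strongest reply is that the text does not say who the sponsor is or what it does. A reader might infer that the sponsor is the party running the trial. That is a common meaning of the word, but no section available says so. If the sponsor is a funder with no part in conduct, there is less for interim knowledge to influence.

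A reader might also infer that the sponsor's knowledge would reach the bedside and shift the oxygen and discharge decisions that make up the primary event. The documents do not support this. Treatment is prescribed by attending physicians, oxygen support follows medical judgment, and investigators collect the outcomes. Nothing says that the sponsor treats or scores patients, or that committee members may pass results to those who do. Care providers already know each patient's allocation, so open-label bias exists in any case. An added effect would need a leak that the protocol does not describe.

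Nor is the independence of the advice simply lost. The committee also has clinicians and a biostatistician, its role is advisory, and the analysis is done independently.

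Finally, session rules are commonly set in a charter, and {21a} leaves the meeting agenda and template to the committee. The absence of such rules from a journal article is not an error.

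All of this stands and limits the point. It does not answer it. The issue is not a missing detail but an explicit sentence that makes the sponsor a member of an unblinded committee. A charter could soften the consequence, but the sentence would still say the opposite. Knowing individual allocations, as the physicians do, is also different from knowing the accumulated comparison between arms, which is what interim confidentiality protects.

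**Conclusion.** The point holds in a limited form. As written, the sponsor would see primary-outcome results by arm at half of the events and possibly before the analysis plan is final. This undercuts the purpose of the independent statistician and compromises, without removing, the independence of the committee's advice.

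The remaining half of the events follows from the trigger alone. The figure of about 70 (72 with 180 patients) rests on the censoring assumption above. It counts events, not patients still to be recruited, since some of those events will come from patients already randomised. No bias can be calculated from the document, and none is claimed to have occurred. How serious the matter is depends on the sponsor's role in conduct, which the sections available do not state. Access to the results and the conflict in membership are present whatever that role is. The sentence should be changed.

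**What to change.** Amend the membership sentence in {21a} along these lines:

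> The DSMC consists of clinicians and at least one biostatistician, all independent of the sponsor. Interim results by arm are seen only by these members, in closed session. The sponsor may attend open sessions, where data are pooled over arms, and receives only the committee's recommendation.

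Add to {17a} that the unblinded status applies to these independent members only.

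The cost is small. The protocol wording changes and goes to the ethics committee as an amendment, and the sponsor gives up direct access to interim results. A replacement member may be needed if too few independent members remain, so it cannot be assumed that no extra person is required. Requiring independence from the investigators as well would go further, and nothing available shows whether the present clinicians would meet that test. Sample size, endpoint and timing of the look are unaffected. If the sponsor was never meant to see arm-level results, the sentence still needs the same correction.

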### Adverse event reporting and harms {22}

The project investigators will prepare reports according to the adverse event data collected by themselves.

Both adverse events (AEs) and serious adverse events (SAEs) will be collected throughout the follow-up period, from the time of informed consent to day 28 of evaluation. The serious adverse events that occur after day 28 will be evaluated by the investigators and the DSMC to determine whether they have any relation with the experimental drug under study.

All SAEs will be accompanied by study physicians until there is total or at least significant improvement.

Following the International Conference on Harmonization Guidelines for Good Clinical Practice, all AEs will be investigated in detail and included in an electronic CRF (REDcap). The information collected will include the following: start date of possible AE, reported signs and symptoms, relationship between the reported event and the drugs studied, outcome of the adverse event, and the dates on which the data were evaluated by the DSMC.

### Frequency and plans for auditing trial conduct {23}

An audit of this trial will be carried out by an independent group with the aim of identifying problems more promptly in any of the phases of this protocol and thus correct them as soon as possible, in accordance with the principles of the International Conference on Harmonization Guidelines for Good Clinical Practice.

This group should make an evaluation before starting the trial to verify that the study coordinators are able to carry out the inclusion and the management of the data appropriately. During the trial, they should also check whether the entire study protocol is occurring appropriately, including recruitment, enrollment, and allocation of participants; adherence of hospital staff to interventions and health care procedures; reporting of harms; and data collection and management. There should be one visit of the monitoring group to the Clinics Hospital of the University of Campinas during the study to check whether such criteria are being fulfilled and also with an educational function in order to encourage all those involved in the research to adhere to the protocol.

More detailed information about the audit process of this trial can be found in the Manual Audit.

### Plans for communicating important protocol amendments to relevant parties (e.g., trial participants, ethics committees) {25}

Any change in the study protocol involving the studied population, study design, eligibility criteria, patient allocation, randomization process, outcomes, sample size, statistical data analysis, procedures of study, or administration of study data should generate protocol amendments, which will always be submitted for analysis by the Ethics Committee/institutional review board (IRB). The changes will only be implemented after approval by this committee, unless this change may harm the patient’s safety.

All protocol amendments will also be sent to the DSMC.

### Dissemination plans {31a}

The study results will be published in conferences, a pre-print database, and peer-reviewed journal publications.

We also hope that the data will be disseminated to the health authorities and the lay audience, so that we can have wide public knowledge of these results. We will prepare a one-page report, which will be informative and visual, to be delivered to the patients who participated in the study.

## Discussion

So far, there are no specific treatments for COVID-19. There is great concern regarding the duration of hospital treatment required in severe forms, because in the context of a pandemic, prolonged hospitalization means that health services may not be able to meet the demand generated by the disease. Therefore, we consider that one of the main aims for the treatment of severe pneumonia caused by COVID-19 should be to reduce the length of stay. Recent studies have shown that pulmonary inflammation and extensive lung damage in SARS patients can lead to more severe conditions [1, 2]. Furthermore, researchers have shown that SARS-CoV-2 binds to the angiotensin 2-converting enzyme (ECA2) to gain access to cells. This enzyme is fundamental both in the inactivation of angiotensin II (ANGII) and in the inactivation of bradykinin. The accumulation of bradykinin in the lungs is a common effect after the use of ECA2 inhibitors. In animal models, ECA2 inactivation leads to severe pneumonitis, and bradykinin inhibition fully recovers lung function and structure [9].

Several previous clinical trials have already shown the efficacy of both C1 esterase and icatibant, both bradykinin inhibitors, for use in a condition called hereditary angioedema. Considering our hypothesis that the release of bradykinin could be responsible for the hyperinflammatory state of the airway in SARS-CoV-2 infection and that its inhibition could reduce such inflammation, we imagine that the use of such drugs would help reduce the complications caused by COVID-19 pneumonia and consequently reduce the duration of hospitalization. This would mean a great gain for the health system since it would allow greater patient turnover, besides reducing the chance of secondary infections inherent in a long hospitalization.

We chose to define our study population as patients hospitalized due to COVID-19 pneumonia precisely because we considered that patients with severe disease would be those who would benefit most from reduced hyperinflammatory status. The choice of outcome as the time to event (improvement of the ordinal scale of seven items or hospital discharge) was based on previous clinical studies (LOTUS and Remdesivir trial). We consider that this outcome will allow us to evaluate whether in fact the drugs tested contribute to a reduction of morbidity over time. In addition, it will help us to infer whether the use of intervention could mean a shorter stay. As the outcome is the same as in previous studies, we will also have the benefit of literature comparison.

We will be using a multi-arm design to increase study effectiveness and reduce costs. C1 esterase and icatibant were selected because they are the only two drugs that inhibit the bradykinin pathway that have been approved for use in patients in Brazil. In addition, they require short-term use (only 4 days) and already have a safe and effective dose established for use in hereditary angioedema.

We chose standard care as the comparator only because we believe that there are no clinical trials with sufficient impact to indicate any specific treatment for COVID-19 pneumonia. Therefore, the use of any specific drug in our study would be unethical. The use of a placebo is not possible, since the development of two placebos identical to the interventions, one of intravenous infusion and another of subcutaneous infusion, would require a lot of time and would significantly increase costs. Blinding is also not possible in this study. We cannot blind the assisting physician either because of safety issues or because she/he will be responsible for prescribing the experimental drug. In addition, the absence of a placebo would make it much easier for the patient to guess that she/he was selected for the intervention. This is the first attempt at evaluating the use of bradykinin pathway inhibitors in pneumonia caused by COVID-19. We believe that the results will be of great importance for hospital management of the disease at the global level.

## Trial status

Version 2.0, November 17, 2020, recruiting; the expected end date is April 2021.

## Data Availability

The final data of the study and the generated database will be available for access by all investigators and the entire scientific community.

## Abbreviations

ACE2: Angiotensin 1-converting enzyme 2
ACE: Angiotensin-converting enzyme
AE: Adverse event
ALT: Alanine aminotransferase
ANG II: Angiotensin II
AST: Aspartate aminotransferase
Beta-HCG: Beta human chorionic gonadotropin
C1: Complement 1
COVID-19: Coronavirus disease 2019
CRF: Case report form/clinical research flowchart
CRP: C-reactive protein
CT: Computed tomography
CTCAE: Common Terminology Criteria for Adverse Events
DSMC: Data Safety Monitoring Committee
ECG: Electrocardiogram
ECMO: Extracorporeal membrane oxygenation
eCRF: Electronic case report form
FAPESP: Sao Paulo Research Foundation
FiO_2_: Fraction of inspired oxygen
HIV: Human immunodeficiency virus
ICU: Intensive care unit
IRB: Institutional review board
ITHACA: COVID-19 Treated by c1 esterase inHibitor And iCAtibant
IU: International unit
LOTUS: A trial of LOpinavir-RiTonavir in adUlts hospitalized with Severe COVID-19
LPS: Lipopolysaccharide
MV: Mechanical ventilation
NIV: Non-invasive ventilation
PaO_2_: Partial pressure of oxygen
PI: Principle investigator
ReBec: Brazilian Clinical Trials Registry
REDCap: Research Eletronic Data Capture
RCT: Randomized clinical trial
RNA: Ribonucleic acid
RT-PCR: Reverse transcription PCR
SAE: Serious adverse event
SAP: Statistical analysis plan
SARS-CoV: Severe acute respiratory syndrome coronavirus
SOFA: Sequential organ failure assessment
SOPs: Standard operation procedures
SpO_2_: Partial saturation of oxygen/pulse oximeter oxygen saturation
SUS: Sistema Único de Saúde (to refer to Brazilian Health System)/integrated health system
TTCI: Time to clinical improvement
USA: United States of America
USP: United States Pharmacopeia
UTN: Universal trial number
WHO: World Health Organization
